### Randomization and allocation concealment

2.5

A member of Sichuan evidence-based Medicine Center of TCM, who does not participate in subsequent trials, uses SAS 9.2 software (SAS Institute Inc., Cary, NC) to generate 92 random serial numbers. Randomization is performed after screening and baseline evaluation, and eligible T2DM-CAP subjects will be randomized in a 1:1 fashion to receive 1 of 2 treatments. The group numbers are provided in continuously numbered, sealed envelopes made of carbonless paper. The envelopes will be held by a research administrator who will not be directly involved in the recruitment or follow-up of any participants. The administrator provides the subjects with their group number on the day of inclusion. Consequently, the subjects, clinical researchers, data managers, outcome assessors, and statisticians do not know the allocations, which not be revealed until the study is completed.

### Blinding

2.6

This trial is a double-blind design and participants and statisticians will be blinded during the trial period. Both placebo granules and Chinese herbal granules are produced, packaged, and labeled by the same manufacturer to ensure identity in specification and appearance. In addition, the research team will be trained not to interflow with the participants about their probable treatment group allocation. Only an emergency occurs, such as serious adverse event, can the investigator inform the main investigator to decide whether to expose the blind.

### Diagnostic criteria

2.7

Participants must meet the Western medicine diagnostic criteria for type 2 diabetes (Table 1),^[21]^ CAP (Table 2)^[22]^ and the TCM syndrome diagnostic criteria of pulmonary-splenic asthenia and accumulation of phlegm-dampness syndrome (Table 3).^[35]^ The determination of syndrome differentiation are determined independently by 2 appointed deputy physicians of TCM.

**Table 1 T1:**
[figure not shown]
Diagnostic criteria for type 2 diabetes mellitus^[21]^.

**Table 2 T2:**

Diagnostic criteria for community-acquired pneumonia ^[22]^.

**Table 3 T3:**
[figure not shown]
Diagnostic criteria for traditional Chinese medicine differentiation of pulmonary-splenic asthenia and accumulation of phlegm-dampness syndrome^[35]^.

### Eligibility criteria

2.8

#### Inclusion criteria

2.8.1

Participants have a history of type 2 diabetes and are hospitalized with confirmed CAP.Participants meet the criteria for pulmonary-splenic asthenia and accumulation of phlegm-dampness syndrome in TCM.Participants aged 18 to 70 years, no gender limitations.Participants can complete this study and all tests.Participants provide informed written consent and volunteer to participate in the trial.

### Exclusion criteria

2.9

Patients with other coexistent pulmonary diseases (e.g., bronchiectasis, pulmonary edema, chronic obstructive pulmonary disease, tuberculosis, or interstitial lung disease).Patients with severe comorbidities, such as malignant tumors, infectious diseases, coronary heart disease, mental abnormality, or patients whose laboratory data indicating severe systemic disease (such as liver and kidney dysfunction).Women who are breastfeeding, or pregnant.Allergies for experimental drugs or CHM.Patients have participated in other clinical trials in the 1 month preceding the trial.

### Termination and withdrawal criteria

2.10

All participants are informed of their right to terminate and withdraw from the trial. The reason will be recorded in case report forms (CRFs). The criteria for stopping treatment and withdrawing from the research are:

participants suffered severe adverse reactions related to the medication, and the researcher believes that they should stop taking drugs;participants suffered from another serious illness that required treatment during the study;participants’ condition deteriorate severely and even require respiratory support therapy;poor compliance, the actual dose is less than 80% of the prescribed dose.

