#### Primary outcome

3.3.1

Disease outcomes include cure, significant effect, effective, and ineffective. The main result is the total clinical effectiveness after treatment (day 14) of the 2 groups, that is, the sum of cure rate, apparent efficiency and effective.

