### Compliance

3.5

Once subjects are randomized, investigators will try to follow them throughout the study. At each visit, adherence to intervention are monitored and subjects are required to return all unused packs of granules. Furthermore, subjects will be served with continuous support in subsequent stages, such as post-discharge rehabilitation advice.

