### Statistical analysis

3.8

Statistical analysis will be performed at the Sichuan evidence-based Medicine Center of TCM using Statistical Package for the Social Sciences version 22.0 (SPSS 22.0, Chicago, IL). Intention-to-treat and per protocol sets are applied to analyse the efficacy of modified BXXXD. A safety analysis set is used to assess the safety of the study. Missing values are estimated using the principle of the last observation carried forward, with the data from the last study follow-up used as the final results.

Categorical data are tabulated with frequencies or percentages, and continuous data are reported as median or mean ± standard deviation. For the sociodemographic data and baseline variables are conducted using analysis of variance and Chi-squared test. To compare the variables of the same group before and after treatment, a paired *t*test is used. Repeated measures analysis of variance is used to compare the differences among the 2 groups. All statistical tests are bilateral tests and *P* values < .05 is regarded as statistical significance.

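### One list governs both stopping the granules and leaving the research, so the clearest treatment failures can lose their day-14 result and be filled in by LOCF

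*Protocol article*

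**What the plan says.** Section 2.10 (Termination and withdrawal criteria) introduces its list with "The criteria for stopping treatment and withdrawing from the research are". Four items follow:

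- drug-related severe reactions: "participants suffered severe adverse reactions related to the medication, and the researcher believes that they should stop taking drugs"
- another serious illness that needs treatment
- a patient's "condition deteriorate severely and even require respiratory support therapy"
- "poor compliance, the actual dose is less than 80% of the prescribed dose"

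Section 3.3.1 sets the primary outcome: "The main result is the total clinical effectiveness after treatment (day 14) of the 2 groups". It is binary in effect, with three grades of success against *ineffective*. No earlier assessment of it is listed. Only secondary outcomes have earlier visits, such as the symptom score and pneumonia severity index at days 4 and 8 (3.3.2).

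Section 3.8 says "Intention-to-treat and per protocol sets are applied to analyse the efficacy of modified BXXXD" and "Missing values are estimated using the principle of the last observation carried forward".

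Section 3.5 (Compliance) states a general aim: "Once subjects are randomized, investigators will try to follow them throughout the study".

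**The concern.** Stopping a study drug and leaving a study are separate events, and intention-to-treat analysis depends on keeping them apart. Section 2.10 attaches both to every item on its list. At least two items, deterioration and drug-related reactions, are tied to outcome or treatment. The result would therefore be missing because of how the patient fared, although it could have been observed.

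A patient who worsens to the point of respiratory support is the plainest *ineffective* result this trial can produce. Nothing in the article says that such a patient is scored that way, or that the day-14 assessment still takes place. The intention-to-treat set nominally keeps the patient, but the value is imputed from a status that may predate the deterioration.

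If both arms are handled alike, both look better than they are, and a real difference shrinks because the arm with more failures loses more of them. If the arms are handled differently, a difference can appear where there is none. A later analysis plan could change the imputation, but it could not recover day-14 assessments that were never made.

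**Working it through.** **Inputs from the article.** Effective rates of 73% (control) and 93% (experimental), 82 patients needed, 92 enrolled after a 10% loss allowance, 80% power at one-sided 5% (2.4); 1:1 allocation, so 46 per arm (2.1); two-sided tests at 0.05 (3.8). Power is given both ways because 2.4 and 3.8 differ on sidedness.

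**The plan's own figure.** Unpooled normal approximation, one-sided 5%, 80% power:

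n per arm = (1.645 + 0.842)² × (0.73×0.27 + 0.93×0.07) / 0.20² = 40.5, rounded up to 41, so 82 in total. Then 82 / 0.90 = 91.1, rounded up to 92. Both figures reproduce.

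**Assumption.** The article gives no withdrawal rate. Let *s* be the share of true failures withdrawn under 2.10, the same in both arms. True failure rates are 0.27 and 0.07. Two ways of handling these patients bracket the problem:

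- Dropped: difference = 0.93/(1 − 0.07*s*) − 0.73/(1 − 0.27*s*)
- Carried forward as effective: difference = 0.20 × (1 − *s*)

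| *s* | Withdrawn of 92 (46 × 0.34*s*) | Dropped | Carried forward as effective |
|---|---|---|---|
| 0 | 0 | 20.0 points | 20.0 points |
| 10% | 1.6 | 93.66 − 75.03 = 18.6 | 18.0 |
| 25% | 3.9 | 94.66 − 78.28 = 16.4 | 15.0 |
| 50% | 7.8 | 96.37 − 84.39 = 12.0 | 10.0 |
| 75% | 11.7 | 98.15 − 91.54 = 6.6 | 5.0 |

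At *s* = 50% the withdrawals are 46 × 0.135 = 6.2 control and 46 × 0.035 = 1.6 experimental. That is 7.8 of 92, or 8.5%.

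**Power** (exact binomial power of the pooled z, i.e. chi-squared, test):

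| Scenario | n per arm | One-sided 5% | Two-sided 5% |
|---|---|---|---|
| No withdrawals | 46 / 46 | 85% | 77% |
| *s* = 10%, carried forward (75.7% vs 93.7%) | 46 / 46 | 81% | 72% |
| *s* = 50%, dropped (84.4% vs 96.4%) | 40 / 44 | 60% | 47% |
| *s* = 50%, carried forward (86.5% vs 96.5%) | 46 / 46 | 57% | 45% |

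**Unequal handling with no true effect.** Assume 73% in both arms, with 25% of failures withdrawn in control and 50% in experimental.

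- Dropped: 0.73/(1 − 0.135) − 0.73/(1 − 0.0675) = 0.844 − 0.783 = 6.1 points in favour of the herb.
- Carried forward as effective: 0.27 × (0.50 − 0.25) = 6.75 points.

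**The case against.** The strongest reply is that the article can be read more kindly. Section 2.10 never says that the day-14 assessment is cancelled, its first item speaks only of stopping the drug, section 3.6 stops only the intervention after a severe adverse event, and 3.5 promises an effort to follow everyone. This shows that continued follow-up may be intended. It does not remove the explicit wording on leaving the research, which a general aim under Compliance does not override. It also shows that the article is not consistent about what stopping means.

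Second, carrying forward need not turn a failure into a success. The team that withdraws a deteriorating patient has seen the deterioration and must record the reason. If a rating of *ineffective* were entered then, that rating would carry forward. But no text requires an outcome rating at withdrawal.

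Third, dropping patients is not the stated intention-to-treat analysis. That is correct for the analysis as named. The case is still relevant, because no earlier primary-outcome rating is listed for LOCF to carry and because such patients would ordinarily fall outside a per-protocol set.

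Fourth, the larger shares may be too high. *Ineffective* can include patients who merely did not improve, and a 75% share (12.7% of 92) exceeds the planned 10% loss. This stands: the 75% row is an extreme, and the 10% row is a fair milder case. The 85% baseline also assumes no other loss; at 41 per arm it is 81%.

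Fifth, the false-benefit example needs unequal withdrawal in a trial planned as double-blind. It shows a possible direction of bias and is not a prediction. The calculations also cover only withdrawn failures and do not quantify the compliance or intercurrent-illness items.

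**Conclusion.** The concern holds and should be fixed. The stated rules, taken together, allow the clearest failures to lose their day-14 result and to be mis-scored or left out. This comes from what the article fixes and is not a detail left to another document.

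The size cannot be determined from the article. Under the assumption of equal shares in both arms, the effect runs from slight (18 points and 81% one-sided power at a 10% share, carried forward as effective) to serious (10 to 12 points and 57% to 60% at a 50% share). The 50% case is about 8 patients, which lies inside the planned loss allowance and so would not look abnormal. The carried-forward figures assume that every withdrawn failure keeps a favourable earlier status, so they are the adverse end of that route. With equal handling the bias is towards no effect. A false benefit of 6 to 7 points needs the unequal shares assumed above.

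**What to change.** - Limit the section 2.10 criteria to stopping the granules. Limit leaving the study to withdrawal of consent for follow-up.
- State that the day-14 assessment is done on every randomised patient who still consents, whether or not the granules were stopped. This brings 2.10 into line with 3.5 and 3.6.
- Add one scoring sentence to 3.3.1 or 3.8: severe deterioration, respiratory support or death before day 14 counts as *ineffective* in the intention-to-treat analysis, and no earlier status is carried forward for these patients.
- Use the under-80% dose rule only to define the per-protocol set.

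The cost is a minor wording amendment and a few extra assessments at a visit that already exists, some of them after discharge. The sample size does not change.

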### Test drugs

2.11

Test drugs are modified BXXXD and BXXXD mimetic agent (placebo), provided by the Sichuan Green Pharmaceutical Technology Development Co., Ltd. (Sichuan, China). Whole ingredients of modified BXXXD are Rhizoma Pinelliae Praeparata (Fa ban xia) 15 g, Zingiberis Rhizom (Gan Jiang) 10 g, Scutellariae Radix (Huang qin) 15 g, Coptidis Rhizoma (Huang lian) 6 g, Ginseng Radix et Rhizoma (Ren shen) 15 g, Jujubae Fructus (Da zao) 10 g, Radix Et Rhizoma (Zhi gan cao) 10 g, Ephedrae Herba (Ma huang) 15 g, Armeniacae Semen Amarum (Ku xing ren) 15 g, Poria (Fu Ling) 15 g, and Citri Reticulatae Percarpium (Chen pi) 15 g. The pharmaceutical company mixes, cooks, and sprays the herbs medicines in the prescription to form granules. These granules are packaged into small single-dose sachets, each weighing 10 grams. The placebo is made from starch with no active ingredients. By adding a diversity of food pigments, the placebo is as close to the real particles in appearance and taste as possible.

## Interventions

3

### Treatment plan

3.1

Both groups are given basic treatment^[21–22]^: on the basis of lifestyle interventions (diabetes diet, proper exercise), short-acting insulin subcutaneous injection is preferred to ensure that blood glucose can be controlled within the target range (FPG 6.1–7.8mmol/L, 2hPG 7.8–10 mmo/L). After infection control, oral hypoglycemic agents or insulin are selected according to blood glucose levels. Subjects are given second-generation cephalosporins empirically for anti-infection, while those who were allergic to cephalosporins are given Levofloxacin and then given sensitive antibiotics based on the results of drug sensitivity. Antibiotics are used for 7 to 14 days depending on the patient's condition.

#### Experimental group

3.1.1

Subjects in the experimental group take modified BXXXD granules (10 g) orally twice daily for 2 weeks, after breakfast and supper.

#### Control group

3.1.2

Subjects in the control group are given placebo granules (10 g) twice daily for 2 weeks.

#### Concomitant medications

3.1.3

Subjects are not permitted to take other CHM during the entire study.

### Collection of blood for metabonomics

3.2

The subject blood samples are collected in a centrifuge tube and placed at 37°C for 1 hour for coagulation and stratification. The supernatant is centrifuged and transferred to a freezing tube, and stored at –80°C for preservation. All samples are destructed after use.

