**Methods::**

We propose a double-blind, placebo-controlled, randomized superiority trial.

A total of 92 participants with T2DM-CAP will be randomly allocated at a 1:1 ratio to either the experimental group, which will receive modified Ban-Xia-Xie-Xin-Decotion and basic treatment, or the control group, which will receive basic treatment only. The study duration will be 14 days. The primary outcome will be the total clinical effective rate. The secondary outcomes are traditional Chinese medicine symptom score scale, pneumonia severity index, usage time of antibiotic, time required for blood sugar to reach the required level, frequency of hypoglycemia, and chest CT. Liquid chromatograph-mass spectrometry method will be used to explore the blood metabolism profiles of the subjects, to explore the pathogenesis of T2DM-CAP and the mechanism of CHM on T2DM-CAP. Adverse events will also be evaluated.

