#### Secondary outcomes

3.3.2

1)**TCM symptom score scale (**at days 4, 8, and 14).2)**Pneumonia severity index** (at days 4, 8, and 14).3)**usage time of antibiotic** (at days 6, 10, and 14).4)**time required for blood sugar to reach the required level (**at days 2, 4, 6, 8, 10, 12, 14).5)**frequency of hypoglycemia (**at days 2, 4, 6, 8, 10, 12, 14).6)**laboratory examination:** including white blood cell count, percentage of neutrophils, C-reactive protein and procalcitonin **(**at days 4, 8, 14).7)**chest CT (**at days 14).8)** Exploratory outcome:** Differences in blood metabolomics between the 2 groups after treatment **(**at days 14).

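### Metabolomics blood stands unseparated at 37°C for one hour before it is spun, so labile metabolites in the frozen serum no longer reflect circulating blood

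*Protocol article*

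**What the plan says.** Section 3.2 of the protocol article sets out the handling in a fixed order.

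- **Collection:** "The subject blood samples are collected in a centrifuge tube".
- **Hold:** the tube is "placed at 37°C for 1 hour for coagulation and stratification".
- **Separation and storage:** "The supernatant is centrifuged and transferred to a freezing tube", and then kept at -80°C.

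The article states no cooling, no metabolic inhibitor and no separation from the cells before the hour at 37°C is over.

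These samples serve item 8 of section 3.3.2, labelled exploratory and taken at day 14: "Differences in blood metabolomics between the 2 groups after treatment". The abstract gives the purpose of the LC-MS profiles as "to explore the pathogenesis of T2DM-CAP and the mechanism of CHM on T2DM-CAP". Item 6 of section 3.3.2 lists laboratory tests "including white blood cell count, percentage of neutrophils, C-reactive protein and procalcitonin" at days 4, 8 and 14, so cell counts are outcomes on the same day as the metabolomics sample.

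**The concern.** Warmth helps blood to clot, but body temperature also keeps red cells, white cells and platelets working. While the serum stays in contact with them, they use up some small molecules and release others. Freezing stops further change but does not undo what happened in the hour before. The sample therefore records circulating metabolism plus an hour of metabolism in the tube.

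Two uses of the data suffer. The first is the pathogenesis and mechanism aim, which needs the profile to describe the patient's blood. A shift made in the tube in glucose- or energy-related features could be read as a feature of the disease, and that reading is tempting in patients who have both diabetes and infection. The second is the day-14 comparison between arms. Patients differ in cell counts, so the shift differs from patient to patient and adds noise to a comparison with at most 46 patients per arm (92 randomised 1:1).

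This is not a detail left to another document. The article itself prescribes the temperature, the duration and the order of steps.

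**Working it through.** The plan states no figure on this point, so there is none to reproduce. The check is a reading of the sequence, followed by an illustration of what the sequence can and cannot do to the comparison.

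**Inputs from the protocol article**

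- Hold before separation: 37°C for 1 hour (section 3.2).
- Material held: blood as drawn, since centrifugation comes after the hold (section 3.2).
- Use of the samples: between-group difference at day 14, exploratory (section 3.3.2, item 8).
- Handling by arm: one rule for all samples (section 3.2), with concealed allocation and identical-looking granules (sections 2.5 and 2.6).

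**Inputs not in the article (assumptions, for illustration only)**

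- r, the fraction of a labile metabolite lost in the hour: 3% to 15%.
- k, cell activity in one arm relative to the other: 1.0 (equal), 1.2 or 1.5.

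**Step 1: effect on the level.** Measured level = true level × (1 - r). At r = 0.03 the sample reads 97% of the true value, and at r = 0.15 it reads 85%. This applies in both arms, so it affects any reading of the profile as circulating blood. Metabolites released by the cells move the other way.

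**Step 2: effect on the between-arm ratio when the true ratio is 1.** Spurious ratio = (1 - r × k) / (1 - r).

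| r | k = 1.0 | k = 1.2 | k = 1.5 |
|---|---|---|---|
| 3% | 0.97/0.97 = 1.000 | 0.964/0.97 = 0.994 | 0.955/0.97 = 0.985 |
| 15% | 0.85/0.85 = 1.000 | 0.82/0.85 = 0.965 | 0.775/0.85 = 0.912 |

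With equal cell activity there is no spurious difference, however large the loss. With unequal activity one appears, and its size depends wholly on r and k. The article supplies neither.

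**Step 3: noise between patients.** Suppose two patients have the same true level, and one loses 3% while the other loses 15%. Their measured values stand in the ratio 0.85/0.97 = 0.876. The spread comes from the tube alone. How much spread the trial would see depends on how r varies between patients, which the article does not give.

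**The case against.** The strongest reply is that the shift is largely shared. Allocation is randomised and concealed, every sample follows the same rule, and the outcome is a between-group difference. A shift common to both arms mostly cancels, as the k = 1.0 column shows. This stands, and it limits the point.

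A reader might go further and infer that the hold will produce a false drug effect, because white cells and neutrophils are outcomes that treatment could change. The documents do not support that. Section 3.3.2 lists the counts but predicts no difference between arms. By day 14 both arms will have had 7 to 14 days of antibiotics (section 3.1), and even the control arm is assumed to reach a 73% effective rate (section 2.4). A gap in mean counts at day 14 is possible but not established. Any figure for the resulting artefact would need a count difference and a per-cell rate, and the article gives neither.

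It can also be said that the article plans general LC-MS profiles and names no glycolytic metabolite as a target, and that the outcome is exploratory. Both are true. Metabolites that are insensitive to contact with cells may remain usable. This lowers the weight of the point but does not remove it: the profiles are the trial's stated route to mechanism, and the labile features in them would still be distorted.

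**Conclusion.** The point holds in a limited form. As written, section 3.2 leaves serum on metabolically active cells at body temperature for an hour. Labile metabolites in the frozen sample will not match circulating blood. That weakens the pathogenesis and mechanism aims directly and adds between-patient noise to the exploratory day-14 comparison.

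The size cannot be derived from the documents. The illustration rests on an assumed loss of 3% to 15% per hour. Under it, levels are misread by that amount in both arms, while the between-arm ratio stays at 1.000 unless cell number or activity differs by arm. A between-arm bias is therefore conditional.

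Nor should a reader infer that the trial's main result is at risk. The total clinical effective rate, the clinical secondary outcomes and the safety assessment do not use these samples and are unaffected.

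**What to change.** In section 3.2, keep serum as the sample type and replace the 37°C, one-hour hold with one fixed rule for all samples that is shorter and cooler. One example is clotting at room temperature for a fixed period of about 30 minutes, then cold centrifugation and immediate freezing. The exact time is for the laboratory to set, since the documents give no basis for it; what matters is less time on the cells at a lower temperature, the same for everyone. Record draw-to-spin time for each sample.

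Flag samples already processed at 37°C as a separate batch, and do not interpret glycolysis-linked features from them as drug effects. Do not try to repair the comparison by adjusting for the day-14 white cell count. That count is measured after randomisation and may itself respond to treatment, so adjusting for it could remove part of a real effect or introduce bias.

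The change needs no extra visit, sample or patient. It costs somewhat tighter timing for ward and laboratory staff, and samples taken before the change will not be directly comparable with those taken after it.
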